**Methods/Design:**

The study is designed as an RCT. The web support consists of three parts: 1) evidence-based information, 2) a self-care diary, and 3) communication with peers. The primary outcome is general well-being evaluated with the Well-Being Questionnaire short version (W-BQ12) and diabetes management evaluated with the Diabetes Empowerment Scale, short version (SWE-DES). Women attending six hospital-based antenatal care centers in Sweden are invited to participate. The inclusion period is November 2011 to late 2014. The allocation of participants to web support (intervention group) and to usual care (control group) is equal (1:1). In total, 68 participants in each group will be needed to reach a statistical power of 80% with significance level 0.05.

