### Sample size estimation

Sample size estimation in this RCT is based on the two primary outcome variables: 1) general well-being measured by the Well-Being Questionnaire (W-BQ12) and 2) diabetes management measured by the Swedish Diabetes Empowerment Scale (SWE-DES). In order to detect a clinically relevant difference of 1.25 in well-being between the intervention group and the control group, 68 subjects will be needed in each group to reach a statistical power of 80%, assuming a SD of 0.40 in each group, with a significance level 0.05. Similarly, to detect a difference of 0.2 in diabetes management, 68 subjects will be needed in each group to reach a statistical power of 80%, assuming a SD of 2.5 in each group, with a significance level 0.05. A total sample size of 160 has been chosen to compensate for a probable 10% loss to follow-up.

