### Participants and recruitment

A total of 160 participants will be recruited to the MODIAB-Web study performed in western and central Sweden. The enrollment started in two centers in November 2011 in the western region of Sweden. Successively, another four centers from the central part of Sweden were included; one was added in June 2012, another one in October 2012 and finally two more were included in June 2013. All study centers are hospital based. A list of participating study centers can be obtained upon request from the corresponding author.

One diabetes midwife in the antenatal care unit at each hospital-based study center identifies all pregnant women with type 1 diabetes. If women registered at the study units meet the inclusion criteria and do not meet any exclusion criteria, the midwife provides them with oral and written information about the study early in their pregnancy. If a woman agrees to participate in the study, she signs an informed consent form.

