### Withdrawal criteria

Participants are withdrawn from the trial after randomization if they meet the following criteria: miscarriage, termination of pregnancy, intrauterine fetus death during the pregnancy or infant death within six months after birth.

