### Statistical analyses plan

The full analysis set, Intention To Treat population (ITT population), consists of all randomized patients who had at least one follow-up measurement. The Per-Protocol population (PP population) consists of all patients in the ITT population without any significant protocol deviations. The PP population is defined at the clean-file meeting before the database is locked. Primary efficacy analyses will be performed on our two primary variables general well-being (W-BQ12) total score and diabetes empowerment (SWE-DES) total score, both at six months after delivery between the two randomized groups using Fisher’s non-parametric permutation test on the full analysis set (ITT population), two-sided test on significance level 0.025. If significant differences in baseline variables are found between the two randomized groups, a complementary analysis of covariance (ANCOVA) will be performed adjusted for these baseline variables. Last observation carry forward (LOCF) will be applied from two months if the six months value is missing.

Statistical analyses will be conducted using SPSS, version 16.0, and SAS, version 9.2 (Cary, NC). All tests will be two-tailed and conducted at 5% significance level.

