### Strength and limitations

The strength of this study is that a generic web-based support is always accessible, can complement health care independently of differences in ‘usual care’ provided in each center, and places no extra burden on healthcare professionals. However, the use of the web-based support is voluntary, which might have an impact on the uptake of the intervention. We use the CONSORT-EHEALTH Checklist [29] to report on intervention adherence and measures undertaken to encourage the use of the web-based support; for example, an SMS reminder every second week. One limitation of the study is that it is not feasible to blind members of the healthcare team to group allocation, a common problem in clinical trials. Another limitation is that a higher percentage of women with type 1 diabetes suffer from miscarriage, which will prolong the data collocating period. Additional centers have been included to increase the data collection rate.

To conclude, we have described a protocol with a randomized controlled design in order to systematically evaluate the effectiveness of a web-based support to women with type 1 diabetes during pregnancy, childbirth and early motherhood. If proven effective, it will provide evidence for a modern and accessible complementary health-care intervention.

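### The stated 80% power is calculated at 0.05 but the primary tests use 0.025, where 160 women give about 77% per outcome after the stated 10% loss; the loss allowance itself is also misdescribed

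*Protocol article*

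**What the plan says.** All references are to the protocol article.

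- **Abstract, Methods/Design:** "68 participants in each group will be needed to reach a statistical power of 80% with significance level 0.05".
- **Sample size estimation, W-BQ12:** "In order to detect a clinically relevant difference of 1.25 in well-being between the intervention group and the control group", the section states that "68 subjects will be needed in each group to reach a statistical power of 80%, assuming a SD of 0.40 in each group", at significance level 0.05. For SWE-DES it gives a difference of 0.2 with an SD of 2.5, and again 68 per group, 80% and 0.05.
- **Sample size estimation, total:** "A total sample size of 160 has been chosen to compensate for a probable 10% loss to follow-up". Participants and recruitment repeats the target: "A total of 160 participants will be recruited to the MODIAB-Web study".
- **Statistical analyses plan:** the primary comparison at six months after delivery is made for both outcomes with Fisher's permutation test on the ITT population, "two-sided test on significance level 0.025". A missing six-month value is replaced by the two-month value.
- **Withdrawal criteria:** "Participants are withdrawn from the trial after randomization if they meet the following criteria", namely miscarriage, termination, intrauterine death, or infant death within six months.
- **Exclusion criteria:** a randomized woman who miscarries in the first trimester and conceives again during data collection returns to her original arm.
- **Strength and limitations:** "a higher percentage of women with type 1 diabetes suffer from miscarriage, which will prolong the data collocating period"; centers were added to speed up data collection.

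**The concern.** The power statement and the primary test use different significance levels. The analysis divides 5% between two primary outcomes, while the sample size gives each outcome the full 5%. A reader who takes 80% from the abstract or the sample size section is therefore reading the power of a test that the plan does not make its primary one.

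Two further features make the figure hard to rely on. The SDs as printed cannot lead to 68 for either outcome. And the step from 136 evaluable women to 160 does not match the loss rate given for it, while a second loss route that the protocol itself creates is not mentioned in the allowance. At stake is how a non-significant result would be read: the chance of missing the target difference on a given outcome is larger than the 20% the article implies.

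**Working it through.** **Inputs.** From Sample size estimation: differences 1.25 (W-BQ12) and 0.2 (SWE-DES), SDs 0.40 and 2.5, 68 per group, power 80%, level 0.05, total 160, loss 10%. From Statistical analyses plan: two-sided 0.025 for each primary outcome. Allocation is 1:1.

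**1. Trying to reproduce the 68.** Normal approximation: n per group = 2(z₁₋α/₂ + z₀.₈₀)²/d². At two-sided 0.05, (1.960 + 0.842)² = 7.849.

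- SDs as printed, W-BQ12: d = 1.25/0.40 = 3.125, so n = 15.70/9.77 = 1.6, or 2 per group.
- SDs as printed, SWE-DES: d = 0.2/2.5 = 0.08, so n = 15.70/0.0064, or 2,453 per group.
- SDs exchanged: 1.25/2.5 = 0.5 and 0.2/0.40 = 0.5. Both outcomes then give n = 15.70/0.25 = 62.8, or 63 per group; the t-test solution is 63.8, or 64.

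Only the exchanged SDs come near 68, and they give the same number for both outcomes, as the article does. Dividing 64 by a rank-test efficiency of 0.955 gives 67.0, which would round up to 68, but the article states no such factor. With 68 per group the t-test power at 0.05 is 82.5%.

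**2. The level used for the primary tests.** At two-sided 0.025, (2.241 + 0.842)² = 9.505, so n = 2 × 9.505/0.25 = 76.0, or 77 per group. The t-test solution is 77.3, or 78 per group. That is 156 evaluable women, so only 4 of 160 could be lost before power falls below 80%.

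**3. From 68 per group to 160.** 2 × 68 = 136. 136/0.90 = 151.1, or 152 with equal groups. 136 × 1.10 = 149.6, or 150. Neither is 160. Working back, 136/160 = 0.85, which is a 15% allowance. With 10% lost, 160 × 0.90 = 144 remain (72 per group), 8 more than 136. Those 8 women (5% of 160) are what is left for the planned withdrawals before fewer than 68 per group remain.

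**4. Power per outcome with 160 randomized.** Two-sample t-test, d = 0.5. The article gives no withdrawal rate, so total loss is shown as an assumed range.

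| Total loss | Per group | Power at 0.05 | Power at 0.025 |
|---|---|---|---|
| 0% | 80 | 88.2% | 81.5% |
| 10% | 72 | 84.6% | 76.8% |
| 15% | 68 | 82.5% | 74.1% |
| 20% | 64 | 80.1% | 71.2% |
| 25% | 60 | 77.5% | 68.0% |

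**The case against.** **The surplus is safe.** The article says 160 was chosen to compensate for 10% loss, not that it was computed from it, and rounding 152 up to whole randomization blocks of ten gives 160. That explanation is an inference, but the direction is not in doubt: 160 is more than 10% loss requires. A reader might infer that the arithmetic slip leaves the trial too small. The documents do not support that.

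**Pregnancy loss need not break the 80%.** A reader might also infer that the unmentioned withdrawals by themselves take power below 80%. At 0.05 that would need more than about 20% total loss, and the article gives no rate. It also does not say that the 10% excludes withdrawals. Re-entry after first-trimester miscarriage recovers some women, data collection is to be prolonged and centers were added. Nor does the article say whether withdrawn women count towards the 160 or are replaced. All of this stands. Re-entry is only partial, though: it does not cover later losses or women who do not conceive again in time.

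**Carry-forward.** A woman with a two-month but no six-month value still contributes to the primary analysis, so non-return at six months alone does not reduce the analysed number. This stands, and the losses in the table should be read as women with neither value. It does not help a woman who loses the pregnancy, because she has no two-month postpartum value to carry forward.

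**The closing 5% statement.** The analysis section ends by putting all tests at the 5% level, which could be read as covering the primary tests. But the sentence specific to the two primary outcomes sets 0.025, and the specific rule is the natural one to follow. If 5% was intended for each, the section contradicts itself and the answer still has to be written down.

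**The 68 against 64.** This difference is small and conservative, and it may reflect a rank-test allowance. I make no point of it.

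**Conclusion.** The concern holds in this form: at the level set for the primary tests, the design does not deliver the stated 80% per outcome. Power is 76.8% under the article's own 10% loss and 74.1% at the 68 per group it calls sufficient, shortfalls of about 3 and 6 percentage points. No assumed withdrawal rate is needed for this. Withdrawals add to the shortfall, to 71.2% at 20% total loss.

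The loss allowance is a lesser matter of description. The 160 matches 15% total loss rather than 10%, the difference is 8 extra women, and the planned withdrawals are not mentioned.

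The figures assume d = 0.5, which rests on reading the printed SDs as exchanged; t-test power as a stand-in for the permutation test; equal losses in the two arms; and power counted for each outcome separately, as the sample size section does.

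**What to change.** Without changing enrolment, in Sample size estimation:

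1. Confirm and correct the SD assigned to each outcome (apparently 2.5 for W-BQ12 and 0.40 for SWE-DES).
2. Replace 80% at 0.05 with the power that 160 gives at two-sided 0.025: about 77%, 74% and 71% per outcome at 10%, 15% and 20% total loss.
3. State that 160 allows 15% total loss (24 women), including withdrawals for pregnancy or infant loss, while keeping 68 per group. Do not claim that 68 per group gives 80% at the primary test level.

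The power sentence in the abstract needs the same correction, and the closing 5% sentence in Statistical analyses plan should exempt the primary tests.

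The cost is a few sentences and a less favourable stated power, by roughly 3 to 9 percentage points over that range of loss. No further women, visits or analyses are required.

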### Participants and recruitment

A total of 160 participants will be recruited to the MODIAB-Web study performed in western and central Sweden. The enrollment started in two centers in November 2011 in the western region of Sweden. Successively, another four centers from the central part of Sweden were included; one was added in June 2012, another one in October 2012 and finally two more were included in June 2013. All study centers are hospital based. A list of participating study centers can be obtained upon request from the corresponding author.

One diabetes midwife in the antenatal care unit at each hospital-based study center identifies all pregnant women with type 1 diabetes. If women registered at the study units meet the inclusion criteria and do not meet any exclusion criteria, the midwife provides them with oral and written information about the study early in their pregnancy. If a woman agrees to participate in the study, she signs an informed consent form.

### Inclusion criteria

Participants have to fulfill the following criteria to be eligible for inclusion: literate and Swedish-speaking pregnant women over 18 years of age with a diagnosis of type 1 diabetes and registered at one of the six participating study centers, who have provided written informed consent beforehand.

### Exclusion criteria

Eligible participants will be excluded if they meet the following criterion: miscarriage before randomization, previously randomized to either the intervention or control group in the ongoing study, except randomized women who miscarry (first trimester) and are pregnant again during the data collection period; those who miscarried earlier but are now pregnant will be connected to the group to which they were randomized in the earlier pregnancy (intervention or control), and all data will be collected on this new pregnancy.

### Withdrawal criteria

Participants are withdrawn from the trial after randomization if they meet the following criteria: miscarriage, termination of pregnancy, intrauterine fetus death during the pregnancy or infant death within six months after birth.

### Ethical considerations

The study adheres to the principles of the Declaration of Helsinki [15] and has been approved by the Ethics Committee of Gothenburg, Sweden (No. 659-09). Written consent will be obtained from each participant after she has received written and verbal information about the study and before the baseline assessment. All participants have the right to withdraw from the study at any time.

### Randomization and allocation concealment

Participants are randomly allocated to the intervention group (IG) with web support with evidence-based information, self-care diary and communication with pregnant women with type 1 diabetes in addition to usual care, or to the control group (CG) provided only the usual care. Randomization is performed before baseline assessment.

The randomization is prepared with a unique code that consists of a first code letter identifying each center, a second code letter identifying which group it belongs to, and intervention (IG) or control (CG) followed by a consecutive number. Baseline questionnaires are marked with unique code letters/numbers and placed in a closed envelope. The envelopes are produced in blocks of ten, five IG and five CG. This is prepared by the research group and includes the single blind number. The allocation of participants will be equal (1:1) in blocks of ten for each of the six centers. After informed consent is received, the responsible diabetes midwife at each center gives the included woman a closed envelope and registers her personal information and the obtained code letters/numbers. The key connecting the code with the woman’s personal information is stored in a safe location at the study center, in accordance with that specific hospital’s policy. All data files used for data analysis contain the code number as the only source of identification.

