### Blinding

Due to the nature of this trial it is not possible to blind the participants. Nevertheless, the diabetes midwives in charge of the random allocated sequence at the centers are not involved in the preparation of the envelopes, the use of web-based support or in the statistical analyses.

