### Follow-up period and outcome measurement

During the 18-month follow-up period, the primary and secondary outcomes are tested at baseline, early pregnancy (T0), late pregnancy (T1), two months after childbirth (T2), and six months after childbirth (T3) (see Figure 2). Outcome measures are collected by questionnaires mailed to the participants in IG and CG. Participants who have not returned the questionnaire within ten days receive a phone call from the study coordinator or project assistant as a gentle reminder.

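### Self-reported T0 scores are probably completed after the woman knows her group, so they should not trigger or adjust the complementary ANCOVA

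*Protocol article*

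**What the plan says.** The order of events is fixed in the protocol article, Randomization and allocation concealment: "Randomization is performed before baseline assessment". The same section describes the code on the baseline form as containing a center letter and "a second code letter identifying which group it belongs to, and intervention (IG) or control (CG) followed by a consecutive number". It continues: "Baseline questionnaires are marked with unique code letters/numbers and placed in a closed envelope". On handover it says: "After informed consent is received, the responsible diabetes midwife at each center gives the included woman a closed envelope".

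The Blinding section adds: "Due to the nature of this trial it is not possible to blind the participants".

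Follow-up period and outcome measurement has the primary and secondary outcomes measured at T0 as well as later, by questionnaire: "Outcome measures are collected by questionnaires mailed to the participants in IG and CG". A reminder call follows if a form is not returned within ten days.

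Under Exclusion criteria, a randomized woman who miscarries in the first trimester and becomes pregnant again during data collection keeps her earlier arm, and "all data will be collected on this new pregnancy".

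The Statistical analyses plan section makes the primary analysis a permutation test of six-month scores between the randomized groups. It adds a complementary ANCOVA, adjusted for whichever baseline variables differ significantly between the groups.

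**The concern.** A baseline covariate is safe to adjust for because randomization cannot have changed it. A self-rated score given after an unblinded woman has learned her group does not have that protection. Being pleased with the web support, or disappointed at not getting it, could move T0 well-being or empowerment differently in the two arms.

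The plan uses baseline in two linked steps: a significance test decides whether to adjust, and the variables that differ are then adjusted for. If T0 has reacted to allocation, the first step fires for a reason other than chance. The second step then conditions on a variable measured after randomization. Any change-from-baseline result inherits the same problem.

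The form may also be filled in days after handover, and the article does not bar web access in that interval. For a re-entering woman in the intervention group, the new T0 may follow web use in the earlier pregnancy.

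**Working it through.** **Does T0 follow knowledge of allocation?** Set side by side, the sections give this sequence: consent; handover of an envelope with a group-coded baseline form; completion of the form by a woman who cannot be blinded. The Ethical considerations section requires only that consent precede baseline. No section keeps the allocation hidden until T0 is complete. The article mentions a single-blind number without explaining it, and this does not show concealment from the woman. If T0 is instead mailed like the later questionnaires, it still comes after randomization.

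**Where can T0 enter?** Not in the primary permutation test, which compares six-month scores without adjustment. It can enter the baseline balance test, the complementary ANCOVA and any change score.

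**Inputs.**
- Trigger level: 0.05, the general level in the Statistical analyses plan section.
- n = 72 per group: 160 planned, less 10% loss, gives 144, or 72 per arm.
- Assumed, because the article gives neither: T0 shift g = 0.1 to 0.3 SD (intervention minus control) and T0-to-six-month slope r = 0.5, with 0.3 to 0.7 as a range. The six-month scores are assumed not to be changed by whatever moved T0.

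**ANCOVA bias.** Let d be the true effect in SD and D the observed T0 difference. Given D, the expected six-month difference is d + r(D − g). Subtracting the adjustment rD leaves d − rg. The bias is −rg whatever D turns out to be, so it is the same in the trials where the trigger fires.
- g = 0.1, r = 0.5: −0.05 SD
- g = 0.2, r = 0.5: −0.10 SD
- g = 0.3, r = 0.5: −0.15 SD
- Over r = 0.3 to 0.7: from −0.03 (0.3 × 0.1) to −0.21 (0.7 × 0.3)

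If g is negative, each sign reverses and the ANCOVA favors the intervention.

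**Trigger rate.** The noncentrality of the two-sample t-test is g√(n/2), and √(72/2) = 6.

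| g (SD) | Noncentrality | Baseline test significant, 72 per group | 68 per group |
|---|---|---|---|
| 0 | 0 | 5% | 5% |
| 0.1 | 0.6 | 9.2% | 8.9% |
| 0.2 | 1.2 | 22.2% | 21.2% |
| 0.3 | 1.8 | 43.2% | 41.2% |

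**Simulation check** (68 per arm, 4000 runs, two-sided 0.025, r = 0.5; ANCOVA applied in every run; a t-test stands in for the permutation test).

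| g | ANCOVA estimate, true d = 0.50 | ANCOVA power | ANCOVA rejection, d = 0 | Unadjusted estimate, true d = 0.50 | Unadjusted rejection, d = 0 |
|---|---|---|---|---|---|
| 0 | 0.499 | 0.859 | 0.023 | 0.501 | 0.021 |
| 0.1 | 0.449 | 0.778 | 0.034 | 0.500 | 0.023 |
| 0.2 | 0.402 | 0.663 | 0.060 | 0.502 | 0.022 |
| 0.3 | 0.353 | 0.537 | 0.103 | 0.504 | 0.025 |

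With g positive and d = 0, the ANCOVA estimates are negative, so the excess rejections go against the intervention. The unadjusted comparison does not move.

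**Relative to the target.** A bias of 0.05 to 0.15 SD is 10 to 30% of 0.50 SD. The article does not print 0.50 SD. It follows only if the two SDs under Sample size estimation are exchanged (1.25/2.5 = 0.2/0.40 = 0.50). As printed, the ratios are 1.25/0.40 = 3.1 and 0.2/2.5 = 0.08.

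**The case against.** The strongest objection is that the trial's conclusion does not depend on T0. The primary test is unadjusted, and the ANCOVA is complementary and runs only if triggered. The article also does not name the T0 W-BQ12 and SWE-DES scores among the baseline variables to be tested. All of this stands and limits the point to supporting analyses. Still, both scales are measured at T0, and nothing in the wording keeps them out of the test and the adjustment.

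It can also be said that knowledge of allocation at T0 is inferred. The article does not say that the woman can decode the letter, or when she is told her group or given web access. That is fair, and the point should be put as probable. The article contains nothing that points to concealment from her.

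The sizes are assumptions, and only their arithmetic is firm. The direction is unknown.

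Four stronger readings may tempt a reader, and the article supports none of them:
- That the primary result is biased. T0 is not an input to it.
- That every baseline comparison is compromised. Diabetes duration is fixed, and HbA1c comes from medical records; neither is open to this reporting bias.
- That adjustment necessarily hides a real benefit. A shift in the other direction would exaggerate it.
- That women are lost to the primary analysis by declining T0 once they know their group. The analysis set requires only one follow-up measurement, and differential non-return of T0 is possible but not shown.

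**Conclusion.** The point holds in a limited form. The article randomizes before baseline and delivers a group-coded T0 form to women who cannot be blinded, so the self-reported T0 scores are probably exposed to allocation. The unadjusted six-month primary test is not affected. The significance-triggered ANCOVA, the baseline balance check and change-from-baseline results on the self-reported scales can be biased in either direction, by slope times shift.

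Under the assumed shift of 0.1 to 0.3 SD and slope 0.5, the ANCOVA estimate moves by 0.05 to 0.15 SD, and the trigger fires in about 9 to 43% of trials instead of 5%. These figures illustrate what could happen. They are not evidence that a shift has occurred. The number of re-entering women is unknown, so their contribution cannot be sized. The point is worth acting on because the trial was still recruiting at submission and the correction is cheap; it does not threaten the primary conclusion.

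**What to change.** **Women still to be enrolled.** After consent, have the T0 questionnaire completed and handed in before the allocation envelope is opened. Mark the form with a neutral study ID without a group letter. It must carry some identifier, because the code is the only link in the data files. The envelope then holds the allocation but not the baseline form.

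**Women whose T0 followed allocation, including all re-entrants.** Do not use self-reported T0 scores to trigger or adjust the ANCOVA. A re-entrant's T0 from her first enrolment does not solve this if it was also completed after allocation. Adjust instead for pre-specified variables that allocation cannot alter, such as center, diabetes duration and record-based early-pregnancy HbA1c if it was sampled before allocation. One model cannot drop a covariate for only some women, so the trial-wide ANCOVA should leave T0 scores out. A T0-adjusted analysis can be reported separately for women enrolled under the new order. The primary test needs no change.

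**Cost.** A slightly longer enrolment step, repacking of unused envelopes and a protocol amendment. T0 will have been collected in two ways across the trial, and the report should say so and give the numbers under each. Leaving T0 out also gives up its precision gain: with a clean T0 and r = 0.5, simulated ANCOVA power was 0.86 against 0.74 unadjusted (68 per arm, d = 0.50 SD). If few women remain to be enrolled, the change to the ANCOVA is the part that matters, and it needs no new data collection.

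### The study code appears to carry the arm into the analysis files used to define the per-protocol set, and fixed blocks of ten per centre make some allocations foreseeable

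*Protocol article*

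**What the plan says.** All of the coding and envelope procedure is in the protocol article under Randomization and allocation concealment.

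- **The code.** It has a letter for the centre, then "a second code letter identifying which group it belongs to" (intervention or control), then a running number.
- **Where the code goes.** "Baseline questionnaires are marked with unique code letters/numbers and placed in a closed envelope". For the analysis: "All data files used for data analysis contain the code number as the only source of identification".
- **The blocks.** "The envelopes are produced in blocks of ten, five IG and five CG", and "The allocation of participants will be equal (1:1) in blocks of ten for each of the six centers".
- **Who handles the envelope.** After consent, the centre's diabetes midwife "gives the included woman a closed envelope and registers her personal information and the obtained code letters/numbers". Under Participants and recruitment, the same midwife identifies the pregnant women with type 1 diabetes at her centre and informs those eligible.
- **Stated separation.** Under Blinding, the midwives take no part in preparing envelopes, in using the web support or in the statistics. No comparable separation is stated for data entry, data review or the clean-file meeting.
- **The judgement made before lock.** Under Statistical analyses plan: "The PP population is defined at the clean-file meeting before the database is locked". The PP set leaves out women with significant protocol deviations.

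**The concern.** There are two separate weaknesses.

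**Arm visible in the files.** Defining the PP set before lock is meant to keep knowledge of results by arm out of the exclusions. That protection is weakened if the identifier on each record shows the arm. What counts as a significant deviation is a judgement, and here it could be made woman by woman with the arm in view. Members of the research group also review the entered data and moderate the intervention's forum.

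**Foreseeable allocation.** The midwife who decides whom to inform, and when, builds up a list of past arms at her centre because she registers each code. In a block of fixed size, once one arm's five envelopes are gone, the rest are known. A closed envelope opened after consent protects the single draw. It does not protect the decision to approach a woman now, later or not at all. The participants are unblinded and the primary outcomes are self-reported, so any selective enrolment would enter the comparison directly.

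**Working it through.** **Disclosure through the code (no arithmetic).** The section defines one code made of letters and a number, and the group letter is part of it. Questionnaires carry the letters and numbers, so data entry sees the arm. The analysis files carry the code as sole identifier, and no arm-free recoding is described. The clean-file meeting therefore works on records whose identifier shows the arm, unless the consecutive number alone was meant.

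**Foreseeability.** The article states no figure to reproduce.

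Inputs from the article: block of 2m = 10 (m = 5 per arm), blocks separate in six centres, total 160. Assumption: the midwife knows past arms at her centre and the block size.

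1. *Certain allocations in a complete block.* There are C(10,5) = 252 equally likely orders. The number of allocations known with certainty is 1, 2, 3, 4 or 5 in 140, 70, 30, 10 and 2 of them. The mean is (140 + 140 + 90 + 40 + 10)/252 = 420/252 = 1.67 of 10, or 16.7%, which agrees with 1/(m+1) = 1/6. At least two are certain in 112/252 = 44.4% of blocks.
2. *Best guess in a complete block* (always name the arm with more envelopes left). Expected correct = m + (4^m/C(2m,m) − 1)/2 = 5 + (1024/252 − 1)/2 = 6.53 of 10, or 65.3%, against 50% by chance.
3. *Whole trial, 16 complete blocks.* 16 × 1.67 = 26.7 certain allocations. This is the ceiling, since incomplete blocks yield fewer.
4. *Whole trial, even split assumed* (27, 27, 27, 27, 26, 26). The first 7 places of a block yield 0.056 certain allocations on average and the first 6 yield 0.008. The total is 4 × (2 × 1.667 + 0.056) + 2 × (2 × 1.667 + 0.008) = 13.56 + 6.68 = 20.2, or 12.6% of 160. Correct guesses: 4 × (2 × 6.532 + 4.087) + 2 × (2 × 6.532 + 3.444) = 101.6, or 63.5%.
5. *Sensitivity: split by months open.* From the opening dates to December 2014 the centres are open 38, 38, 31, 27, 19 and 19 months, 172 in all. In proportion this gives 35, 35, 29, 25, 18 and 18 women. With 0, 0.667, 0 and 0.222 certain allocations in the first 5, 9, 5 and 8 places, the total is 2 × 5.0 + 4.0 + 3.33 + 2 × 1.89 = 21.1, or 13.2%.

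**Effect of varying block sizes.** I simulated 4,000 trials with the even split. The enroller was assumed to know the set of possible sizes but not their order.

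| Block sizes | Certain | Best guess correct |
|---|---|---|
| Fixed 10 | 12.6% | 63.5% |
| Random 8, 10, 12 | 1.7% (about 2.7 of 160) | 63.8% |
| Random 6, 8, 10, 12 | 1.0% | 64.6% |

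Guess accuracy barely moves, because naming the under-represented arm needs no knowledge of the block size. The formula in step 2 shows the same for complete blocks: 68.3%, 66.6%, 65.3% and 64.3% for sizes 6, 8, 10 and 12, which pool to 65.8% against 65.3% for fixed tens.

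**The case against.** **The files may not show the arm.** The article uses letters and numbers for the questionnaires but only a number for the analysis files, and it mentions a single-blind number in the same section. A reader could take the files to hold the consecutive number alone. That is possible, but the section defines a single code and describes no stripped version, so the other reading is more natural. The article never promises blinded analysts. A reader might infer a broken blinding promise, and the text does not support that. Nor does it say that outcomes are displayed at the clean-file meeting.

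**The consequence for the primary result is small.** This stands. The primary comparison is a prespecified permutation test on the ITT set. A reader might also infer that the ANCOVA covariates are picked at will with the arm in view. They are not: the rule is mechanical (baseline variables that differ significantly), the analysis is complementary, and the rule needs group labels of some kind. Recoding also cannot fully mask the PP decisions, since the adherence rule of two logons applies to the intervention group only.

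**Steering is not shown.** This stands too. The midwife is meant to identify every eligible woman early in pregnancy. At 160/172, about 0.9 enrolments per centre-month, there is little room to time entry. Certainty also requires her to know or infer the block size. The article does not say that she does, nor that it is withheld, and it prints the size while recruitment is under way. Selective inviting would depart from the procedure, but nothing in the procedure prevents it.

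**About 27 of 160 certain allocations is tempting but too high.** It needs 16 complete blocks, which six separately blocked centres are unlikely to give.

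**Conclusion.** Both weaknesses hold, with limited reach. On the natural reading, the identifier in the analysis files shows the arm to those who enter data and define the PP population. This affects the credibility of PP exclusions and leaves the prespecified ITT test untouched. It is a badly fixed procedure, not a contradiction.

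Fixed blocks of ten per centre let a midwife who knows or infers the block size foresee 16.7% of allocations in complete blocks. For the trial the figure is about 12.6% (20 of 160) under an assumed even split, or 13.2% if women are spread by months open. Most allocations stay uncertain, and there is no evidence that any midwife steers enrolment. A best-guess accuracy of about 64–65% is a true description of the design, but varying the blocks does not materially lower it.

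**What to change.** **1. Files.** Give the data-entry and analysis files an arm-free study number. Keep the key to arm outside the analysis group until PP exclusions are signed off and the database is locked. Settle all other deviations first, and apply the intervention-only two-logon rule afterwards as a separate step. Run the baseline comparison that selects the ANCOVA covariates with masked A/B labels, which gives the rule the grouping it needs.

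**2. Unused envelopes.** Replace fixed tens with randomly varying block sizes not disclosed to the centres, for example 8, 10 and 12. Expect certain allocations to fall to about 1–2%, and claim that gain only. Smaller fixed blocks would be worse: for blocks of four, the best guess is right (2 + (16/6 − 1)/2)/4 = 71% of the time.

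**Cost.** One recoding step, a new list for the remaining envelopes, and a slightly larger possible imbalance within a centre. Sample size and outcomes do not change.
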